
### Statistical analysis

#### Quantitative data

The initial analysis of data will be performed on an *intention to treat* basis. A baseline descriptive analysis of the sociodemographic data and measured predictive variables will be carried out to ensure comparability between the intervention and control groups (mothers in the first phase and children in the second phase). Intra-group and inter-group differences in main continuous variables will be analysed by Student’s t test or non-parametric tests (Wilcoxon signed-rank test and Mann–Whitney U test) at different measurement times. For qualitative variables, comparisons will be made using Pearson’s chi square test.

Linear mixed-effects models with participant-level random intercepts will be used to study the effectiveness of the intervention and we will consider adjusting for any demographic or predictive variable results that show important differences at baseline. All statistical analyses will be conducted using the STATA 14.0 and IBM-SPSS 24.0 software. Confidence intervals of 95% and the significance level (*p* values) will be reported.

Subsequent to the initial analysis, we will also carry out a *per protocol* analysis in order to identify possible differences to the intention to treat analysis, which may occur as a result of a differential compliance of participants with the research protocol.

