Regarding the weaning period, a new approach called Baby-Led Weaning (BLW), as opposed to the traditional spoon-feeding (SF), has become popular mostly in the United Kingdom and New Zealand [33]. Actually, regarding the Spanish state, a recent study carried out in Galicia shows a general estimated prevalence of BLW of 14% [34]. Although there is not a clear or precise definition, BLW can be characterized as follows: children are the ones feeding themselves, deciding which will be the rhythm and quantity of food to swallow, using their hands, ingesting pieces of food (not purée, or less than 10% of the total ingested food in purée), sharing family meals, and eating the same family-food [33, 35].

BLW has arisen some concerns on parents, caregivers and health professionals, mainly due to the chocking risk [36]. Nevertheless, some authors have reported no difference on the chocking risk between traditional weaning and BLW [37, 38]. Additionally, there is also a concern about the unfulfilment of the energy requirements of the child [33], particularly regarding initial energy intake. However, the available scientific evidence is not strong enough to support this idea [39]. Among nutrients, iron deficiency is the most generally stated worry [40]. Nonetheless, it has been demonstrated that BLW does not increase iron deficiency nor growth faltering [38]. In any case, children’s diet should be as balanced as possible, in order to fulfil all the nutritional requirements and avoid deficiencies. Some paediatricians have manifested their concern about the possible inappropriateness of food offered to the child when following BLW, stating that meals could be high in fat and too salty [39]. Moreover, allergen intake is also a subject of debate, because food selection is baby-led and this could imply less control over allergen intake in a period when children are more susceptible to food allergens [4]. However, some positive aspects have also been pointed out: usually parents following BLW fulfil WHO (World Health Organization) recommendations regarding the start of complementary feeding at 6 month of age, while SF is associated to an earlier weaning [35]. It has also been observed that when following BLW children develop a better ability for satiety responses [41], which constitutes a protection against obesity. Furthermore, BLW has been related to a greater food variety intake or acceptance [39].

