### Sample size

Sample size (*n* = 144) has been estimated taking into account main variable: FV intake achievement (proportion of children who reach recommendations). Accepting an alpha risk of 0.05 and a beta risk of 0.2 in a bilateral contrast, 72 subjects in the first group and 72 in the second are required to detect as statistically significant the difference between the proportion of children who reach recommendations, which for the control group is expected to be 25% and for the treatment group 50%. The final sample size has been increased by 20% in order to accommodate a drop out of 20%.

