### Allocation to groups

Assignment to the control or treatment groups will be conducted according to mothers likings, type of diet and willingness to perform the weaning process traditionally (SF) or following a baby-led approach (see Table 1). Group assignment will be blind for participants.

**Table 1 Tab1:** Distribution of the control (Ctrl) and intervention (I) groups

Groups	Mothers´ diet during last trimester of pregnancy and breastfeeding	Weaning approach	Group codes
1	“Standard” diet as described in National Diet Surveys (Ctrl)	Spoon feeding (Ctrl)	SD_SF
2		Baby-led (I)	SD_BLW
3	High Fruit and vegetable intake (I)	Spoon feeding (Ctrl)	HFV_SF
4		Baby-led (I)	HFV_BLW

*SD* standard diet; *SF* spoon-feeding; *BLW* Baby-Led Weaning; *HFV* high fruit and vegetable

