#### Intervention group

Baseline questionnaires and initial dietary assessment will be the base for group assignment. Once participants are matched to a group, they will be given a code and will be anonymously treated thereafter. Those above the national (Spain) mean consumption of fruits and vegetables (about 414 g/person/day [58]) will be included in the intervention group. During the study, participants will be encouraged and assessed to achieve even a higher FV intake, following the recommendations given by Aune and colleagues of 800 g/person/day [14]. If a significant decrease in FV intake is detected in the participants' diet during the follow-up visits, dietetic assessment will be performed in order to restore the initial intake. With regard to the weaning groups, those better disposed to follow a baby-led approach will be included in the intervention group.

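### Student's t test is named for weaning groups whose sizes are not controlled, so its 5% error rate holds only if group sizes or variances are roughly equal (minor)

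*Protocol article*

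**What the plan says.** Statistical analysis, Quantitative data: intra-group and inter-group "differences in main continuous variables will be analysed by Student’s t test or non-parametric tests", at each measurement time. The non-parametric tests named are the Wilcoxon signed-rank and Mann-Whitney tests. The same section assigns effectiveness to linear mixed-effects models with participant random intercepts, and categorical variables to Pearson's chi-square. The Qualitative data section uses two-way ANOVA for the coded video behaviours.

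Allocation to groups: "Assignment to the control or treatment groups will be conducted according to mothers likings, type of diet and willingness" to wean one way or the other. Intervention group: "those better disposed to follow a baby-led approach will be included in the intervention group". No ratio, quota or cap is stated.

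Sample size: "72 subjects in the first group and 72 in the second are required", so the calculation takes the two groups as equal.

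The only figure for uptake of baby-led weaning (BLW) is in the Background, where a study in Galicia "shows a general estimated prevalence of BLW of 14" per cent. No SD is given for any continuous outcome in either the BLW or the spoon-feeding (SF) group.

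**The concern.** The pooled t test estimates one common variance, and the larger group dominates that estimate. If the smaller group is the more variable one, the standard error is too small and false positives rise. If it is the less variable one, the standard error is too large and power is lost. With equal group sizes the two effects cancel.

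This design does not secure equal sizes, because preference decides who joins which group. Equal spread is not an obvious default either. The Background describes BLW as leaving pace and quantity to the child, and that could make intake more or less variable than under spoon feeding. The direction cannot be known beforehand.

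The promised 95% confidence intervals would be affected too. With normal data, a pooled-variance interval misses the true difference at the same rate as the test falsely rejects.

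**Working it through.** **1. The plan's own figure.** Inputs from Sample size: "Accepting an alpha risk of 0.05 and a beta risk of 0.2 in a bilateral contrast"; the proportion reaching recommendations, "which for the control group is expected to be 25% and for the treatment group 50" per cent; 20% dropout. The pooled two-proportion formula gives

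n = [1.96·√(2·0.375·0.625) + 0.842·√(0.25·0.75 + 0.5·0.5)]² / 0.25² = (1.342 + 0.557)² / 0.0625 ≈ 57.7, so 58 per group.

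58/0.8 = 72.5, against 72 stated. The figure reproduces. It concerns a binary variable, so it says nothing about SDs.

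**2. Splits examined.** Evaluable infants: 144 × 0.8 = 115.
- BLW share 14%: 0.14 × 115 ≈ 16, so 16:99. This borrows the Galicia prevalence as an illustration; it is not the trial's expected split.
- BLW share 30%: 35:80 (assumed).
- BLW share 40%: 46:69 (assumed).
- Near equal: 58:57.

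**3. SD ratio.** r = SD(BLW)/SD(SF) is not in the documents. It is assumed to range from 0.5 to 2.

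**4. Formula.** With n₁ BLW, n₂ SF and SD(SF) = 1:
- true variance of the difference: V = r²/n₁ + 1/n₂
- variance the pooled test uses, on average: P = [(n₁−1)r² + (n₂−1)]/(n₁+n₂−2) × (1/n₁ + 1/n₂)
- approximate error rate: 2·[1 − Φ(1.96·√(P/V))]

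At 16:99 with r = 1.5: V = 2.25/16 + 1/99 = 0.1507; P = (131.75/113) × 0.0726 = 0.0846; √(P/V) = 0.749; rate = 14.2%.

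At 16:99 with r = 0.5: V = 0.0257; P = 0.0654; √(P/V) = 1.594; rate = 0.2%.

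**5. Simulation.** Normal data, equal means, 40,000 trials per cell. False-positive rate of Student's test, in %:

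| Split (BLW:SF) | r=0.5 | 0.67 | 0.8 | 1 | 1.25 | 1.5 | 2 |
|---|---|---|---|---|---|---|---|
| 16:99 | 0.2 | 1.0 | 2.1 | 4.9 | 9.3 | 14.2 | 22.2 |
| 35:80 | 1.3 | 2.2 | 3.2 | 5.2 | 7.1 | 8.9 | 12.3 |
| 46:69 | 2.7 | 3.4 | 4.1 | 4.8 | 6.2 | 7.1 | 8.5 |
| 58:57 | 5.2 | 4.9 | 5.1 | 5.0 | 4.8 | 4.8 | 5.0 |

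Welch's test stays between 4.8% and 5.2% in every cell.

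**6. Mann-Whitney.** At 16:99 it rejects about 7%, 9% and 12% for r = 1.25, 1.5 and 2 (10,000 trials per cell). The named alternative reduces the problem without removing it.

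**7. Mixed model.** With complete data and a common group effect, the default random-intercept model estimates the difference in participant means and takes its standard error from the pooled between-participant variance. It therefore behaves like Student's test on those means. At 16:99 with r = 1.5, a fitted model with three visits (random-intercept and residual variances assumed equal) rejected in 13.1% of 1,500 trials, in line with 14.2% above. No rate was computed for the ANOVA.

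**8. Cost of Welch when variances are equal.** For a true difference of 2.8 standard errors, power goes from 79.3% to 76.0% at 16:99, from 79.1% to 78.5% at 35:80, and is unchanged at 58:57.

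**9. Skew.** With gamma data (SF coefficient of variation 0.6) at 16:99 and r = 1.5 and 2, Student's test gives 13.8% and 21.6%, and Welch's 7.8% and 9.4%.

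**The case against.** *Pooled versus Welch is a detail for the analysis plan.* Partly right. The article does not use the word pooled, and a plan not shown here may specify Welch. But the article does name a test, and in ordinary usage that name means the equal-variance form. This is a comment on a stated method, and it is one reason for keeping the point minor.

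*The t test is not the effectiveness analysis.* True. The mixed model is, and the binary sample-size variable goes to chi-square. But the default mixed model carries the same assumption and shows the same inflation in step 7, so the point is not removed.

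*The large rates are a worst case.* This stands. A reader might infer that the groups will be unequal and that the weaning comparison has a 9% to 22% false-positive rate. The documents do not support that. The 14% is a background prevalence from another region, and volunteers for this study may split quite differently. No SDs are given. Rates of that size need a split near 16:99, unequal SDs, and the larger SD in the smaller group, all together. Unequal size alone leaves the rate at 5%.

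*Welch is not a complete cure.* Also true, as step 9 shows for skewed data.

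**Conclusion.** The point holds in conditional form and is minor. The named test depends on an equal-variance assumption that the design does not protect, because preference-based allocation leaves group sizes open.

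Over assumed SD ratios of 0.5 to 2, the true level of the nominal 5% test is about 0.2% to 22% at 16:99, 1% to 12% at 35:80, and 3% to 8% at 46:69. It is about 5% if either sizes or variances are equal. These figures assume normal data, and both the splits and the SD ratios are assumptions. They show how sensitive the method is and do not forecast this trial's error rate. The sample-size figure is not in question.

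**What to change.** - Replace Student's t test by Welch's for all between-group comparisons of continuous variables. Where intake is strongly skewed, apply it on a log or square-root scale, noting that this changes the quantity compared.
- In the mixed model, allow the residual and random-intercept variances to differ by group, or use robust standard errors with a small-sample correction.
- In the two-way ANOVA, use heteroscedasticity-robust standard errors.

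This takes two or three sentences of text and no extra data. If variances are truly equal, the loss is about 3 points of power at 16:99, under 1 point at 35:80 and none near 1:1. Two limits remain: Welch does not fully correct for strong skew in a very small group, and the robust options for the mixed model and ANOVA were not simulated here, so their performance with about 16 infants in one group should be checked before relying on them.

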#### Qualitative data

The FIBFEC tool will be used for analysis of the video recordings on new food acceptance. Behaviours (reflecting avoidance or approach), facial expressions and rate of acceptance will be blind-coded according to the guidelines offered by the tool [71].

Spearman rho correlations will be performed to search for possible associations between coded variables. Descriptive statistics and two-way analyses of variance (ANOVA) will be used to test the differences in frequencies of behaviours and expressions between intervention and control groups regarding either the mothers' diet (SD vs. HFV) or the weaning method (SF vs. BLW).

### Ethical considerations

Volunteers must sign an informed consent before enrolment in the study, as well as other specific informed consent forms during the study, e.g. regarding children film footage and biological samples (i.e. breast milk). All participants will be free to leave the study at any stage of the project.

The present study has been approved by the Clinical Research Ethics Committee of the Basque Country (PI2019096) on the 25th of September 2019. It will be conducted following the rules of ethics stated by the Helsinki Declaration (52dn WMA General Assembly, Edinburg, Scotland, October 2000), the Standards of Good Clinical Practice and the current Spanish legislation regulating medical research involving human subjects (Royal Decree 223/2004 on clinical trials and Regulation 14/2007 on Biomedical Research). Data will be protected at all times to avoid not permitted use by external personnel. Confidentiality will be respected according to the Regulation (EU) 2016/679 of the European Parliament and of the Council of the 27th of April 2016 on the protection of natural persons (regarding processing of personal data and free movement of such data and the Law 41/2002, of the 14th of November, regulating patient autonomy and rights and obligations of information and clinical documentation. Thus, the data and information generated during the present study will be considered strictly confidential. Participants will be informed of the global results of the study.

## Discussion

The proposed project is a quasi-experimental study because authors consider that the characteristics of the sample and the independent variables do not allow a randomised approach. Authors believe that randomisation could cause problems such as, a low adherence to the assigned diet. Nevertheless, despite the lack of randomisation and with the objective of strengthening the study, steps proposed by the TREND statement for quasi-experimental designs will be followed. Primary care clinicians will help with the recruitment of pregnant women for the study, which will require an important effort to coordinate the recruitment process. Authors are aware that the management of a big (144 women) and heterogeneous sample size may be difficult. Nonetheless, simplifying measures will be set out and possible confounding factors will be controlled. In fact, a 20% dropout-rate has been estimated. However, possible losses when calculating the sample size have been taken into account.

Authors plan to observe children’s eating behaviour using video recordings during meals. In this regard, apart from the ethical implications of the information management (already considered in the project), it will be challenging to obtain well recorded, clear and usable video recordings. In order to facilitate the video recording process, families will receive precise instructions so as to ascertain the above mentioned requirements. We strongly believe that this methodology will provide stronger data as compared to the self-reported methodology, as previously observed by other authors [45].

This study looks for possible associations between the mothers´ whole diet profile, the physicochemical characteristics of maternal milk and food acceptance of infants. To the best of our knowledge, these aspects have never been studied before following the methodology proposed in the present study protocol. In addition to the mother’s diet, the relevance of a BLW approach will also be studied. Indeed, the relative weight of both factors, mother’s diet and weaning, will be characterised.

A relevant aspect of the present proposal is that, although it will be directed from the academic field, it will be executed in coordination with the Primary Care Services of the Basque Public Health Service (Osakidetza) and it will include the infrastructures and participation of the main Health Research Institutes of the Public Health System (Bioaraba, Biodonostia, Biocruces-Bizkaia). The question we would like to answer is: Is it possible to improve children FV intake tackling the mother’s diet during pregnancy and/or breastfeeding? And, is BLW a valid complementary feeding style that could be prescribed from primary care services? If the intervention is effective, it could constitute the basis for future public programs or nutrition guidelines aiming at improving children eating habits by increasing fruit and vegetable intake, which, could, in turn, result in potential health benefits.

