**Discussion:**

If the intervention is effective, this research work would have a high potential to be transferred to future public health programs or nutrition guidelines, as a feasible solution to achieve a higher intake of fruits and vegetables among children.

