#### Control group

Baseline questionnaires and initial dietary assessment will be the base for group assignment and the study participants assigned to the control group will receive the same anonymous treatment as those in the intervention group. Those below the national (Spain) mean consumption of fruits and vegetables (about 414 g/person/day) or/and those who claim to have difficulties achieving the recommended portions will be included in the control group. When a fruit consumption of one standard deviation below the mean is detected, dietetic assessment will be performed in order to encourage, at least, the mean intake. As for the weaning groups, those better disposed to follow a spoon-feeding approach will be included in the control group.

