### Study procedure

Regardless of the group assignment, all participants will receive the current standard recommendations and care. Dietetic guidelines will be explained at the beginning of the study (last trimester of gestation) and after birth to ensure breastfeeding requirements. Intervention groups will receive additional diet recommendations so that they keep to the high fruit and vegetable consumption and to assure safety and a balanced diet along complementary feeding by BLW. The follow-up for the control group will be focused on ensuring a standard fruit and vegetable consumption and reinforcing general dietetic guidelines. Diets of mothers and children will be closely reviewed during the study to prevent deterioration. This implies a time lapse from the third trimester of the pregnancy until children are 18 months old. Follow-up, measurements will be performed on 6th–7th months of pregnancy, before delivery; on the 2nd, 4th, 6th, 12th and 18th months from birth. Figure 1 summarises the study outline.

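### The maternal-diet contrast compares habitual high consumers who receive support with habitual lower consumers, so it can show an association but not that changing a mother's diet improves her child's fruit and vegetable intake

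*Protocol article*

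**What the plan says.** **Question and use of the result.** The Discussion of the protocol article asks "Is it possible to improve children FV intake tackling the mother’s diet during pregnancy and/or breastfeeding" and says that an effective intervention could be the basis for public programmes or guidelines. The Abstract's Discussion says the same of the project as a whole: "If the intervention is effective, this research work would have a high potential to be transferred to future public health programs or nutrition guidelines".

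**Who enters the HFV group, and what it receives.** Under Intervention group: "Those above the national (Spain) mean consumption of fruits and vegetables (about 414 g/person/day [58]) will be included in the intervention group". These mothers are also encouraged to go higher, towards 800 g/day. If intake falls significantly, "dietetic assessment will be performed in order to restore the initial intake". Study procedure gives the purpose of the extra advice: "Intervention groups will receive additional diet recommendations so that they keep to the high fruit and vegetable consumption".

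**Who is a control, and what controls receive.** The Control group section names: "Those below the national (Spain) mean consumption of fruits and vegetables (about 414 g/person/day) or/and those who claim to have difficulties achieving the recommended portions". When fruit consumption one standard deviation below the mean is detected, "dietetic assessment will be performed in order to encourage, at least, the mean intake". Study procedure describes control follow-up as securing a standard intake and reinforcing general guidance.

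**More modest wording elsewhere.** The Objectives section aims to describe a possible impact of maternal diet, and another paragraph of the Discussion speaks of possible associations. Design and Discussion state openly that assignment is not random.

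**The concern.** The diet group is close to a function of baseline intake, which is the very exposure the study says it acts on. A difference between the diet groups would then combine three things: the mother's prior diet, whatever goes with that diet in the household, and the support. The Background itself says that caregivers' eating habits influence the child's food preferences, and the primary outcomes run to 18 months, while the mother's own diet continues. A difference in favour of the HFV group would be expected even if the support did nothing.

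A public programme on maternal diet would try to raise low intakes. The HFV group contains no mother who entered with a low intake and was raised to a high one. If a positive result were passed to guidelines as evidence that acting on maternal diet works, the inference would rest on a comparison that the study does not make.

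**Working it through.** **1. The rules side by side**

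| Baseline maternal intake | Group | Diet support |
|---|---|---|
| Above about 414 g/day | HFV | Keep the high intake, encouraged towards 800 g/day |
| Above about 414 g/day, reports difficulty | Control possible, through the and/or clause | Standard guidance |
| Below about 414 g/day | Control | Standard guidance |
| Fruit one SD below the mean | Control | As above, plus coaching to at least the mean |

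To isolate the effect of the support, one needs mothers of similar baseline intake with and without it. Only the second row offers that, and those mothers are self-selected by reported difficulty. To isolate the effect of raising a low diet to a high one, one needs low-intake mothers offered the high-intake support. No row provides them.

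**2. The plan's own sample size**

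Inputs from Sample size: 25% vs 50%, two-sided alpha 0.05, power 0.80, 20% dropout. The standard two-proportion formula without continuity correction gives 58 per group. Then 58 × 1.2 = 70 and 58 / 0.8 = 73, so the stated 72 is consistent. The figure is not disputed, but it treats the two groups as exchangeable.

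**3. What adjustment for baseline intake would cost**

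Assumptions, not in the document: normal intake, a sharp cut at the mean, linear adjustment, 72 per diet group.

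- Correlation of group with baseline intake: √(2/π) = 0.80.
- Variance inflation: 1 / (1 − 2/π) = 2.75.
- Effective size: 72 / 2.75 ≈ 26 per group. Power for 25% vs 50% is then about 0.46, against 0.88 for 72 per group without adjustment.

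Even this relies on extrapolating a straight line across the cut-off. The and/or clause would soften the figures somewhat.

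**4. Does coaching narrow or widen the exposure gap?**

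Further assumptions: intake is centred on 414 g/day, and the one-SD rule, worded for fruit, applies to fruit and vegetables together. No SD is given, so a range is shown.

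- Mean above the cut: +0.798 SD. Initial gap: 2 × 0.798 = 1.596 SD.
- Share of controls below −1 SD: 0.1587 / 0.5 = 0.317. Their mean is −1.525 SD.
- If all of these reach the mean, the control mean rises by 0.317 × 1.525 = 0.484 SD. The gap becomes 1.596 − 0.484 = 1.112 SD, 30% smaller, provided no HFV mother increases.
- If, in addition, every HFV mother below 800 g/day reaches 800, the gap widens:

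| Assumed SD (g/day) | Initial gap | Only controls respond | Both respond fully | Share of the HFV rise that restores the initial gap |
|---|---|---|---|---|
| 100 | 160 | 111 | 417 | 16% |
| 200 | 319 | 222 | 453 | 42% |
| 300 | 479 | 334 | 508 | 83% |

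For SD 200 with both responding, the group means are about 804 and 351 g/day. The direction depends on compliance in the two groups, which the document cannot tell us.

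**The case against.** The strongest reply is that the protocol is openly quasi-experimental. It gives reasons for not randomising, follows TREND, says that confounders will be controlled, and words its objective as description. Its statements about programmes are conditional, and the Abstract's sentence covers weaning as well. All of this is true and limits the point to the maternal-diet question. It does not remove it: admitting that assignment is not random is different from saying that the support has almost no comparison at equal baseline intake. The Quantitative data section also promises only to consider adjustment.

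Several stronger readings are tempting, and the document does not support them.

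- *No high consumer goes without the support.* The and/or clause can place above-mean mothers in control.
- *An HFV mother is merely held at her entry level.* Restoration is the response to a fall; the same paragraph encourages a rise towards 800 g/day.
- *The control rule shrinks the exposure contrast by 30%.* That needs full compliance in controls and none in the HFV group. With compliance on both sides the gap widens in every row of the table above.
- *The intervention and control rules contradict each other.* Bringing very low consumers to the national mean fits a control group defined by the standard diet, and the trigger names fruit only. What is unclear is which mean is intended.
- *No analysis could help.* A regression-discontinuity analysis could in principle give a local estimate near 414 g/day, but the article describes none, and the and/or clause blurs the cut-off.

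An analysis on achieved intake is also fairly open to challenge, since achieved intake is self-selected too. It can support the main contrast but does not cure the confounding.

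**Conclusion.** The point holds for the maternal-diet question and should be fixed. The contrast between the standard and HFV diet groups estimates the association of habitually high maternal intake plus support with the child's intake and acceptance. It cannot show that changing a mother's diet improves the child's intake, which is what the Discussion asks and what the Discussion, and the diet part of the Abstract, would carry into programmes or guidelines. The Objectives section is closer to what the design can deliver.

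This conclusion rests on the allocation rules as written and needs no distributional assumption. The 2.75-fold variance inflation and the exposure gaps are illustrations under normality. The net effect of the coaching rules on the exposure contrast is unknown. Neither the stated sample size nor the weaning comparison is affected.

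**What to change.** 1. In the Discussion, and for the diet component in the Abstract, word the question and conclusion as the association of habitually high, supported maternal intake versus standard intake with child outcomes, not as the effectiveness of changing maternal diet.
2. Report baseline and achieved maternal fruit and vegetable intake by group, from the food records already scheduled at baseline, in the third trimester and two-weekly after birth (from the second month until complementary feeding starts). Add a supportive analysis on achieved intake, adjusted for baseline intake and its correlates, and label it observational and still open to confounding.
3. State whether the mean in the control coaching rule is a fruit mean or the 414 g/day fruit and vegetable mean, and reconcile that rule with the entry threshold of the intervention group.

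The cost is some wording and one analysis on data already planned. The price is a more modest claim about maternal diet.
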